### Trial design

This cluster randomized controlled trial (RCT) is designed to study the effect of integrated entomological and educational interventions on dengue incidence, adult dengue mosquito density and KAPs regarding dengue risk reduction among students and parents in two townships in Yangon, Myanmar. The rationale for a cluster design is that interventions are area-wide in character, since they will be implemented in schools, rather than targeting individuals. It is not feasible to randomize some individuals within a school to one intervention and other individuals to another. Schools (clusters) will be randomized into an intervention arm and a control arm.

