*Ae. albopictus* (combined) per school or per house collected both indoors and outdoors for 15 minutes at each location (30 min total collection time) using a battery-driven mechanical aspirator. Collections will occur at baseline and once every four months in all schools. A negative binomial regression will be done with the number of mosquitoes as the outcome variable and number of school-visits as the exposure (denominator) variable, i.e., the logarithm of the number of schools as the ‘offset’. A logarithmic link function will be used. Hence, the exponential of the coefficient for arm will be the between-arm ratio in Adult Index (AI) according to the response variable used. Additional analyses of the AI
_S_ will be done by including the baseline value as an additional covariate. Due to the potential skewness of these values, this will be done by categorizing the index as zero, or above or below the median of the positive values.5. 
**Mosquito Adult Index in households (AI
_H_).** This is the same as AI
_S_ except that collections in households will be done for 10 minutes indoors and outdoors, respectively (20 min total collection time). Collections will occur at baseline and once every four months in five selected households per cluster. This index will be calculated and analyzed in the same way as AI
_S_.6. 
**Breteau Index in schools (BI
_S_).** The BI is the number of containers with
*Aedes* immatures/100 schools. It will be calculated at baseline as well as for each of the three follow up time points. This index will be analyzed similarly to the Adult Index.7. 
**Breteau Index in households (BI
_H_).** This BI is the number of containers with
*Aedes* immatures/100 houses. It will be calculated at baseline as well as for each of the three follow up time points. This index will be analyzed similarly to the Adult Index.8. 
**Knowledge, attitudes and practice scores in students (KAP

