_S_).** These are based on sum scores on a scale from 1–10, where ten indicates the highest score. Scores will be calculated at baseline and at each of the three follow up time points. The total score for each of the three KAP components will be added, and the resulting value expressed on a scale from 0 to 10. The average KAP scores for each school will be calculated over all surveys done in the intervention period. These school-level averages will serve as the response variable for a statistical analysis using linear regression. The explanatory variable will be whether or not the school received the intervention.9. 
**Knowledge, attitudes and practice scores in parents (KAP
_H_).** These scores will be calculated at baseline as well as for each of the follow up time points and analyzed in the same way as explained above.10. 
**Behavioral assessments (BA
_S_ and BA
_H_).** A behavioral model will be developed based on the latent variables collected through the survey and validated with structural equation modeling. The model will be evaluated, and a model fit determined, using the following indices: the Comparative Fit Index (CFI) and the Tucker Lewis Index (TLI) (CFI/TLI > 0.90), the Root Mean Square of Approximation (RMSEA) (<0.08) and the Standard Root Mean Square Residual (SRMR) (<0.10)
^
67
^. Two multi-group analyses will be performed using two control variables: control vs. intervention arm and pre- vs. post- intervention. To do so, measurement invariance will be tested and compared through Chen’s cut-off points for the Comparative Fit Index (CFI) and McDonald’s Non-Centrality Index (NCI)
^
68
^. To test change in fit between nested models suggested thresholds of 0.005 for ΔCFI and 0.010 for ΔNCI will be used11. 
**Engagement assessment with students (E
_S_).** The photovoice sub-study contribute to developing an understanding of students’ degree of engagement and perceptions and experiences of being a participant in the intervention through photographs as well as qualitative data including photo discussion sessions. The approach to data analysis will be inductive and include thematic analysis of the transcribed photo discussion sessions involving the students as co-researchers through member checking of the code book to ensure inter-coder reliability. This process is often used to assess the trustworthiness of qualitative research findings
^
69
^.12. 
**Engagement assessment with parents and teachers (E

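### The household mosquito indices (AI_H, BI_H) get a negative binomial model with no defined analysis record and no allowance for catchment clusters; on house or house-visit rows the arm test would be anti-conservative

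*Protocol article*

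**What the plan says.** The unit of allocation is clear from Trial design: "Schools (clusters) will be randomized into an intervention arm and a control arm". Randomization and blinding gives 23 schools per arm.

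Under Data analyses, the adult index in schools (AI_S) gets this model: "A negative binomial regression will be done with the number of mosquitoes as the outcome variable and number of school-visits as the exposure (denominator) variable". The next words restate the exposure as "the logarithm of the number of schools as the ‘offset". With a log link, "the exponential of the coefficient for arm will be the between-arm ratio in Adult Index (AI) according to the response variable used".

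For the adult index in households (AI_H), "Collections will occur at baseline and once every four months in five selected households per cluster", and "This index will be calculated and analyzed in the same way as AI"_S. The two Breteau indices (BI_S, BI_H) are to be handled similarly. Mosquito collections gives the schedule as baseline plus three follow-ups, with a minimum of five houses per school.

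Other outcomes in the same section have a stated unit. Dengue incidence and seroconversion use the number of cases per cluster as the response. For the KAP scores, "These school-level averages will serve as the response variable for a statistical analysis using linear regression".

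**The concern.** In a cluster trial the arm comparison has to be judged against the variation between randomised units, here 46 catchments. For the mosquito indices the article fixes the distribution, link, exposure, arm coefficient and even the categories of the baseline covariate. It gives neither the record nor any device for clustering: no total per catchment, random effect, estimating-equation method or cluster-robust variance.

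Putting household in place of school in the AI_S text gives rows that are houses or house-visits. Each arm then has 23 × 5 = 115 houses, or 115 × 3 = 345 follow-up house-visits, from 23 randomised units. The negative binomial dispersion parameter takes up extra spread between rows. It does not account for correlation between houses of one catchment or between visits to one house. Standard errors would be too small and confidence intervals too narrow.

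Objective 2 and the hypothesis of lower mosquito indices rest on these outcomes. The Sample size section has no calculation for them and relies on large expected mosquito numbers for power, although precision here is limited by the number of catchments and the variation between them.

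**Working it through.** **The plan's own figures.** There is no power, sample size or ICC for the mosquito indices to reproduce. The only ICC used for planning is 0.01, in Sample size. It was chosen for dengue cases on the basis of malaria data (mean 0.003, 95% CI 0.000 to 0.010).

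**What the exposure wording implies.** There are three follow-up visits per school.

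- One row per school-visit: the exposure is 1, and log(1) = 0.
- One row per school, exposure in school-visits: log(3).
- One row per school, exposure in schools: log(1) = 0.

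The two descriptions of the offset are therefore different quantities. With complete, balanced data either is constant and drops out of the arm ratio. They differ once visits are missed or, for households, once some catchments contribute more than the minimum five houses. No household version is given.

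**Effect of ignoring clustering.** Inputs from the documents: m = 5 houses, or m = 5 × 3 = 15 follow-up house-visits, per catchment, and a 5% level (two-sided assumed). The ICC is an assumption throughout.

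Design effect: DE = 1 + (m − 1) × ICC. Actual type I error of a nominal 5% test that ignores it: 2 × [1 − Φ(1.96/√DE)].

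| ICC | DE, m = 5 | Type I, m = 5 | DE, m = 15 | Type I, m = 15 |
|---|---|---|---|---|
| 0.01 | 1.04 | 5.5% | 1.14 | 6.6% |
| 0.05 | 1.20 | 7.4% | 1.70 | 13.3% |
| 0.10 | 1.40 | 9.8% | 2.40 | 20.6% |
| 0.20 | 1.80 | 14.4% | 3.80 | 31.5% |

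Worked example, m = 5 and ICC = 0.10: DE = 1 + 4 × 0.10 = 1.40; 1.96/√1.40 = 1.656; two-sided tail 9.8%. The m = 15 columns use one common ICC for all pairs of visits, which is a simplification, since visits to the same house are likely to be more alike than visits to different houses.

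**Simulation under no effect.** Set-up: 46 catchments, 5 houses, 3 follow-ups, a mean of 2 females per visit, gamma catchment and house effects, house variance 0.3, visit-level shape 0.7, 3,000 runs, Wald test of the arm coefficient. All variance values and the mean are assumed.

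| House-level ICC | House-visit rows | House rows | One row per catchment |
|---|---|---|---|
| 0 | 10% | 6% | 6% |
| 0.08 | 17% | 12% | 7% |
| 0.13 | 22% | 17% | 7.5% |
| 0.21 | 30% | 21% | 7% |

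The first line shows that repeat visits alone inflate the error on house-visit rows. With catchment records and a t reference on 46 − 2 = 44 degrees of freedom, the error is 5.6% to 6.6%. The catchment-level result is less good with log-normal effects (2,000 runs): 7% to 9% up to an ICC of 0.13 and 12% at 0.22, against 18% and 26% for house rows at those two ICCs.

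**The case against.** The strongest reply is that the documents never make the house the row. The household units in Table 2 are a reporting scale: BI_S is expressed per 100 schools although there are only 46. An exposure counted in visits does something only when counts are summed over visits. Carried to households, that reads naturally as a total per catchment with the log of household-visits as offset, which is sound. Every other outcome with a regression on arm uses the cluster or school as its response, so a consistent cluster-level approach may be intended. Multilevel models are declined only for dengue incidence and seroconversion. A detailed SAP is promised before database lock, and layout of secondary outcomes often belongs there.

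Much of this stands. A reader might infer that the plan does treat five houses as independent and that its test is therefore far too optimistic. The documents support neither step: the row is not stated, and no mosquito ICC is given from which a size could be derived. At the one ICC the protocol uses, the error with house rows is only 5.5%. That value is not evidence that mosquito clustering is small either, because it concerns another outcome.

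The reply does not remove the point. The article did not leave the model to the SAP: it wrote one down, restated its exposure as a different quantity, and applied it by reference to data with a further level of nesting. Both the valid and the invalid layout fit that text.

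**Conclusion.** The concern holds in a conditional form. For AI_H and BI_H the analysis record is undefined, the exposure is inconsistent and has no household version, and clustering by catchment is not provided for. If house rows are used, the type I error is about 5.5%, 10% and 14% at assumed ICCs of 0.01, 0.10 and 0.20; with all 15 follow-up house-visits as rows it is about 6.6%, 21% and 32%. If counts are totalled per catchment, the same model comes much closer to its nominal level, though with 46 records it is not exact.

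For AI_S and BI_S the school is itself the cluster. Only repeat visits could matter there, and only if each school-visit is a row, so the concern is smaller.

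These are secondary outcomes and the primary analysis is unaffected. The text should still be corrected, because the article is offered as a basis for future implementation and the ambiguity would be carried along.

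**What to change.** In Data analyses, state for AI_H and BI_H that there is one record per catchment: the total over all follow-up household-visits, with log(number of household-visits) as offset. Alternatively, keep house-level rows and add a cluster random effect, or a variance clustered on the catchment with a small-sample correction for 46 clusters.

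For AI_S and BI_S, state one record per school, the total over follow-up visits, with log(number of school-visits) as offset in place of the log of the number of schools.

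This costs a sentence or two and no additional data. If house-level rows had been intended, confidence intervals for the household indices will be wider.

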### Process evaluation

**Implementation fidelity scores** for both the vector control interventions and the education/knowledge transfer interventions will range from 1–10, where 10 indicates the highest score when implementation of the interventions were executed as intended. The qualitative data collected from teachers’ self-report logbooks will be analyzed using an inductive approach. Principal component analysis will be conducted using implementation fidelity data and outcomes performance from different implementation units of the intervention to estimate the impact of intervention variability on the results.
**Reflection and adaptation.** Qualitative data from in-depth interviews and focus group discussions will be analyzed using an inductive approach. In addition, feedback sessions with participants including teachers, parents and students will be held to share the code book of the themes generated during analysis to ensure a participatory process, as well as to increase the accuracy and enhance the quality of the data analysis.

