^. Outbreaks were recorded in 2009 (22,400 cases), 2013 (20,255 cases and at least 75 deaths), and 2015 (43,845 cases and 140 deaths)
^
29
^. A dengue outbreak occurred in 2017 with 31,000 cases and 192 deaths at the national level
^
30
^. In 2019, Myanmar also experienced an outbreak of chikungunya, with several cases recorded in travelers to the country
^
31
^. In Myanmar, there are more than 45,000 schools with eight million students, making up approximately 17% of the population
^
32
^. Most cases of dengue in Myanmar, occur in children under 15 years old, especially those in the 5–9-year age group
^
33–
35
^. At the time of planning this study, one objective of the National Strategic Plan for Dengue Prevention and Control of Myanmar was to develop a comprehensive integrated training manual and guidelines including community and school-based vector control
^
27
^. This has led to the
*Aedes*-free school program, which includes educational and practical activities.

Considering the global increase in dengue, effective dengue control should not rely on traditional insecticide-based, silver-bullet, top-down approaches
^
36,
37
^. Simple single-intervention approaches as practiced in the past were not successful, for example larval source reduction or fogging. Suitable combinations of site-specific, effective, acceptable, and sustainable interventions need to be assessed for each situation
^
38
^. Therefore, we developed the current project for urban communities in Yangon, Myanmar. We aim to reduce dengue incidence and entomological risk factors, and improve knowledge, attitudes, and prevention practices by applying innovative combinations of school-driven non-insecticidal vector control tools, educational and knowledge transfer approaches by enhancing the school curriculum, building teachers’ capacity; and communicating behavioral change and transfer of knowledge following previous guidelines and recommendations
^
25,
36,
37,
39
^. A process evaluation will be conducted to supplement and strengthen the impact evaluation and to understand the processes and mechanisms of the interventions that can help explain impact or lack thereof.

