### Randomization and blinding

Allocation of interventions will be done after baseline collections (described below). Of the 46 eligible schools, 23 will be allocated to the intervention arm and 23 to the control arm. This will be accomplished by an open public lottery event. At this event, representatives from each school will attend, including regional and township health and educational representatives, teachers, parents, and students. Information about dengue and the goals of the project will be given. The reasons for randomization, its procedures, and the concepts of intervention and control will be explained. Attendees will also have a chance to ask questions about dengue, vector control, health seeking behaviors, personal experiences of dengue, and specific details about the project. The lottery will be carried out as follows. Small pieces of paper, indistinguishable from one another, numbered from 1 to 46, will be folded and placed in non-transparent envelopes and mixed in a bowl. Each number represents a cluster (school) and a list of the schools with their respective number will be consulted during the process. A large screen with the numbered list of school names will be shown above the bowl, visible to everyone. A person not involved in the study, and accepted by all participants, will be selected to make the draw. Two flip boards with large sheets of paper will be placed on either side of the bowl with the heading ‘Intervention’ and ‘Control’ (in Burmese). The first number drawn (representing a specific school) will be assigned to the Intervention arm, the next number/school drawn will be assigned to the Control arm, and so on. Following the draw, the implications of being in either of the two arms will be discussed and the roles of participants, health volunteers, and sub-district hospital staff will be reviewed. By following this lottery scheme, the interventions are allocated at the same time as the sequence is generated, obviating the need for allocation concealment. At this meeting we will take care not to provide any information about planned dengue control interventions that will be used in the trial to participants from the control arm to minimize contamination between the groups. 

The study is unblinded for both participants and data collectors due to the nature of the intervention, e.g., it is not feasible to use placebo interventions of larvivorous fish.

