^ used to catalyze critical dialogue to encourage reflection and generate new understanding of the issue students choose to highlight in their photographs. Teachers’ engagement will be assessed through in-depth interviews (approximately 23 teachers both pre- and post-intervention to include all intervention schools). Additionally, there will be two focus group discussions conducted post-intervention. With teachers, the following topics will be discussed: 1) roles and responsibilities in vector control education/activities; 2) school outreach activities; and 3) operational or social challenges of education and knowledge transfer to the wider community. Parental engagement will be assessed using in-depth interviews held during parent-teacher meetings (approximately 46 parents, two parents per intervention school). This will gauge the effect of the intervention on bi-directional knowledge flow and engagement between schools, households and the wider community. In particular, interview guides for parents will explore five areas relating to community engagement and the social context of the education and knowledge transfer interventions: 1) personal history (migration, poverty, conflict); 2) perceived health problems (dengue/fever concepts); 3) perceptions of vector control activities; 4) involvement in the school outreach interventions; and 5) perspectives and experiences related to community engagement for vector control and prevention throughout the whole intervention
^
58
^.

**
*Process evaluation.*
** A systematic process evaluation in the intervention arm will be conducted to assess implementation fidelity and adaptation, as well as perception of the dengue control interventions. Implementation fidelity, i.e., the extent to which the intervention was implemented as intended will be assessed, as will adaptation, i.e., the extent to which participants introduce changes to the original components/activities of the intervention to address contextual needs and challenges
^
59
^. The conceptual framework for implementation fidelity developed by Carroll
*et al.*
^
60
^ will be applied using specific process evaluation measures (

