Table 3). Implementation fidelity will be assessed using an index score (ranging from 1 to 10) comprising variables that assess intervention exposure, dose, adherence, quality of delivery, program adaptation, and responsiveness. Index score cards will be developed for both the vector control and education/knowledge transfer interventions. The vector control interventions will be assessed through observation in school premises and households during four visits after implementation of the interventions (
Figure 2). The first three visits will be performed during the trial year, a follow-up visit will measure sustainability of the vector control activities. The index score cards for measuring vector control fidelity will include measurements of lid coverage, guppy fish and trap maintenance and waste management.

**Table 3. T3:** Process evaluation measures.

Measure	Description	Unit	Frequency of data collection	Details
Implementation fidelity of the vector control interventions	The extent to which the vector control activities were implemented as intended at schools and in households	Sum scores on a scale from 1–10, where ten indicates the highest score	4 times: - Jul. Year 1, - Nov. Year 1, - Mar. Year 2, - Jun. Year 2.	Assessed by observation and using index scorecards
Implementation fidelity of the education/knowledge transfer interventions	The extent to which the education/ knowledge transfer activities were implemented as intended by teachers	Sum scores on a scale from 1–10, where ten indicates the highest score, logbooks and qualitative data	4 times: - Jul. Year 1, - Nov. Year 1, - Mar. Year 2, - Jun. Year 2.	Assessed by observation and using index scorecards, as well as through logbook data collection
Reflection and adaptation of the intervention components	To develop an understanding of perceptions and experiences related to the education/ knowledge transfer interventions	Logbooks, qualitative data and code book.	2 times: - Nov. Year 1, - Mar. Year 2,	Assessed using teachers’ logbooks and qualitative methods: in-depth interviews and focus group discussions

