^. For the primary analysis, missing data may occur if complete clusters decline to continue in the trial. In this case, the cluster will still be included as long as any data on the primary outcome are available. This does introduce a risk of bias in estimating effectiveness, if loss of clusters is related to performance of the interventions. Dengue incidence in communities will be analyzed using a Poisson regression model. A negative binomial regression will be considered if there will be over-dispersion in the Poisson distribution. The response variable will be the number of dengue cases per cluster and the exposure will be the person-time at risk. Hence, the analysis will yield rate ratios. Multilevel models will not be used for this outcome since the number of cases may be too small for them to be fitted robustly. Statistical significance will be declared at 5% significance level. The 95% confidence intervals will be calculated and reported where applicable. A detailed statistical analysis plan (SAP) will be developed prior to database lock.

**
*Effect of intervention on secondary outcomes*
**

2. 
**Seroconversion rates in schools (SR
_S_).** The proportion of dengue antibody seroconversion in schools will be calculated as the number of seroconversions between the baseline and subsequent follow-ups at four and eight months after the implementation of the interventions divided by observation-days of school populations. The definition of seroconversion is when a participant has converted from being IgG (or IgM) negative during one sampling event to being IgG (or IgM) positive during a second sampling event. Dengue incidence based on seroconversions will be analyzed using a Poisson regression model. A negative binomial regression will be considered if there will be over-dispersion in the Poisson distribution. The response variable will be the number of dengue cases per cluster and the exposure will be the person-time at risk. Hence, the analysis will yield rate ratios. Multilevel models will not be used for this outcome since the number of cases may be too small for them to be fitted robustly.3. 
**Seroconversion rates in households (SR
_H_).** The proportion of dengue antibody seroconversion incidence in a selection of 40 households per school catchment area will be calculated and analyzed in the same way as for schools.4. 
**Mosquito Adult Index in schools (AI
_S_).** This the number of adult female
*Ae. aegypti* and

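### Principal component analysis of fidelity and outcome data cannot estimate how variation in delivery affects outcomes, which is the purpose the protocol gives it

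*Protocol article*

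**What the plan says.** The Process evaluation section that follows Data analyses puts method, inputs and purpose into one sentence: "Principal component analysis will be conducted using implementation fidelity data and outcomes performance from different implementation units of the intervention", in order "to estimate the impact of intervention variability on the results". It names no second step and no model in which fidelity predicts an outcome.

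The Process evaluation paragraphs under Data collection describe how fidelity is measured. It is an index from 1 to 10 built from "variables that assess intervention exposure, dose, adherence, quality of delivery, program adaptation, and responsiveness", and it is collected in one arm only: "A systematic process evaluation in the intervention arm will be conducted to assess implementation fidelity and adaptation". Under Randomization and blinding, "23 will be allocated to the intervention arm and 23 to the control arm", so there are 23 schools with fidelity data if the school is the implementation unit.

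The Introduction says the process evaluation is there "to understand the processes and mechanisms of the interventions that can help explain impact or lack thereof".

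**The concern.** The purpose is an effect-type quantity: how much outcomes differ when delivery differs. That needs a response, a predictor and a slope with its uncertainty. PCA treats all variables alike and returns the directions along which they vary most together. A large shared component says that the variables move together to some degree. It does not say by how many cases, mosquitoes or score points the outcome changes per point of fidelity.

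This would matter most if the trial found no effect. Readers would then ask whether outcomes were better where delivery was better. The sentence quoted is the only quantitative analysis in the article aimed at that question, and as written it would return no estimate and no interval. The trial was terminated, but the article offers the protocol for later use, so the wording may be carried forward.

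**Working it through.** The plan gives no figure for this analysis, so there is none to reproduce. The check asks whether the named method can produce the stated quantity, and what a suitable one could deliver.

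**Inputs**
- Units: 23 intervention schools (Randomization and blinding), taking the school as the implementation unit.
- Fidelity items: six components (Process evaluation under Data collection).
- Significance level: "Statistical significance will be declared at 5% significance level" (Data analyses, primary outcome). Two-sided testing is assumed, since sidedness is not stated.
- PCA on the correlation matrix, i.e. standardised variables (assumed; the article does not say).

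**1. Two variables, by algebra.** For one fidelity score and one outcome with correlation r, the correlation matrix has eigenvalues 1 + |r| and 1 − |r|. The first eigenvector has entries ±1/√2 = ±0.707 for every non-zero r. Simulation with 23 units and 5,000 runs per setting shows the contrast with regression:

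| True correlation | PC1 loadings (absolute) | PC1 share of variance, mean | Regression slope, mean (SD) |
|---|---|---|---|
| 0 | 0.707, 0.707 | 0.586 | −0.001 (0.224) |
| −0.2 | 0.707, 0.707 | 0.616 | −0.196 (0.216) |
| −0.5 | 0.707, 0.707 | 0.748 | −0.504 (0.191) |
| −0.8 | 0.707, 0.707 | 0.897 | −0.803 (0.133) |

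The loadings do not move. The variance share, (1 + |r|)/2, does reflect the strength of the correlation, but it is not a slope, and it averages 0.586 when there is no relation at all.

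**2. Outcome units.** In one simulated data set the outcome was multiplied by 1, 5 and 20. The regression slope went from −0.480 to −2.402 to −9.609. The PCA output was identical each time: share 0.7545, loadings ±0.707. Standardised PCA therefore cannot express an effect in units of the outcome.

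**3. Other analyses in the article.** The models under Data analyses compare arms, or before with after. None has fidelity as an explanatory variable. The structural equation model concerns behavioural constructs, not fidelity. The gap is not filled elsewhere.

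**4. What regression could deliver with 23 schools** (Fisher z, standard error 1/√(23 − 3) = 0.2236)
- Smallest detectable correlation, 80% power: tanh[(1.960 + 0.842) × 0.2236] = tanh(0.626) = 0.56.
- 95% CI for an observed correlation of 0.40: atanh(0.40) = 0.424; 0.424 ± 1.960 × 0.2236 = −0.015 to 0.862; back-transformed, −0.01 to 0.70.

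Regression answers the question asked, but imprecisely.

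**The case against.** The strongest reply is that one condensed sentence in a journal article is being read as a complete algorithm. It does not say outright that fidelity items and outcomes enter one matrix, or that nothing follows the PCA, and a detailed SAP was to be written before database lock. Which outcomes, which covariates and how scores are built are ordinary SAP content, and their absence is no fault. What remains is that the article does commit to a method and does give its purpose, and the two do not match. If the intention was to relate component scores to outcomes, the step that does the estimating is the one left unnamed, and the same rewording is needed.

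A second reply is that the consequence is small. This stands. The analysis is confined to the intervention arm and is not among the outcomes in Table 2. The article also plans logbooks, interviews, focus groups and triangulation, so explaining the result does not rest on PCA alone.

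A third reply is that intervals can be had for PCA by bootstrap. They can, for loadings or eigenvalues, but those are not intervals for an effect of fidelity.

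A reader might also infer that joint PCA would often manufacture an apparent link when none exists. The material does not support this. In simulation with 23 schools, six items sharing half their variance and an unrelated outcome (assumed inputs), about 20% of outcome loadings on the first component exceed 0.2 in absolute value, but only about 4% exceed 0.3. The protocol sets no cut-off, so either rate reflects a choice the plan does not make. Nor is the overlap between null and real relations peculiar to PCA. Against a true correlation of −0.4, the loading and the simple correlation with the mean fidelity score separate the two cases equally well (area under the ROC curve about 0.9 for both). The two measures correlate at 0.95 to 0.99, and regression has only about 42% power. That overlap comes from having 23 units.

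**Conclusion.** The point holds as a mismatch between method and purpose in a supporting, exploratory analysis. PCA on fidelity and outcomes yields neither a change in outcome per unit of fidelity nor an interval for one, and no other analysis in the article supplies it. This rests on what PCA is and on the two-variable algebra for standardised variables, not on any simulated error rate.

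It would be wrong to infer that the trial's effect estimates are compromised: the primary and secondary between-arm analyses do not use this step. It would also be wrong to infer that regression makes the question well powered. With 23 schools as units and two-sided 5% testing, only a correlation of about 0.56 or more is detectable with 80% power. Fidelity is not randomised, so any estimate is an association.

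**What to change.** Reword the sentence in the Process evaluation section, and carry the wording into the SAP, along these lines:

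- Use PCA, if at all, only to condense the fidelity items into a score, leaving outcomes out.
- Among the intervention clusters, regress each outcome on that score with the model type already planned for it: Poisson or negative binomial with its exposure term for dengue cases, negative binomial with its offset for mosquito indices, linear for KAP scores.
- Include the cluster's baseline value where available, and keep covariates few with about 23 clusters.
- Report the slope (or rate ratio) per unit of fidelity with its 95% CI, labelled as an exploratory, non-randomised association.
- State in advance that precision is low, with a smallest detectable correlation of about 0.56 at 80% power.

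The data are those already planned. The cost is slight extra analysis work and an interval that will be visibly wide.
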